#### Baseline

All patients who have consented to participate in the study will complete baseline questionnaires before being told the outcome of randomisation. Baseline questionnaires will record the following information:Sociodemographics (e.g. home postcode, sex, age, ethnicity, employment status)Clinical information (e.g. diagnosis, comorbidities, time since transplant)Current computer usagePatient satisfaction (modified VSQ-9)HRQoL (EQ-5D-5 L)Costs (e.g. healthcare use, travel and personal expenses associated with appointment attendance)

#### Follow-up

Patients will complete patient satisfaction and summary cost questionnaires after each myVideoClinic or standard hospital appointment. For participants on a 3-monthly follow-up schedule, data will be collected at baseline and at 3, 6, 9 and 12 months. For participants on a 6-monthly follow-up schedule, data will be collected at baseline and at 6 and 12 months. For all participants, the 6- and 12-month questionnaires will collect full data on satisfaction, costs (e.g. health service use, travel and personal expenses), IT issues and HRQoL. Patients who also have appointments at 3 and 9 months after baseline will complete shorter questionnaires at these time points, covering satisfaction and costs only. Questionnaires will be sent to patients in both study arms electronically through the myhealth@QEHB system no more than 7 days after each appointment.

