### Recruitment and consent

Prior to each clinic where recruitment is taking place, a member of the clinical team will screen the day’s clinic list to identify eligible patients on the basis of time since transplant and age (inclusion criteria 1 and 2). Patients who meet these criteria will have the study introduced to them at the end of their routine outpatient appointment and their further eligibility assessed against inclusion criteria 3 to 7. The consultant will give eligible patients a Participant Information Sheet and those interested in study participation will have the opportunity to discuss the study with a member of the University of Birmingham research team. The research team will take written informed consent during the clinic from patients who wish to participate and the latter will complete a baseline questionnaire prior to randomisation. Patients who require more time to consider participation will be able to take the study information away and will be contacted by telephone within 7 days by a member of the research team. If a patient agrees to take part over the telephone, a consent form and baseline questionnaire will be posted to them along with a reply-paid envelope for return of the completed documents to the University of Birmingham. Once recruited, participants will stay in the study for 12 months. This will equate to between two and four follow-up appointments since the participants’ usual appointment schedule and frequency will continue to be defined by clinical need regardless of group allocation.

If a patient does not wish to participate in the study, their reason for refusal will be recorded, along with routinely collected information (age, sex and clinic attended). To further understand reasons for participants not taking part, a selection of non-participating patients (*n* = 4) will be invited to take part in a short semi-structured interview (see qualitative study section).

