### Intervention group

Patients randomised to the myVideoClinic group will be sent appointments for their video clinic through the post and will receive standard text reminders about their appointment. Patients will be required to have their clinical tests (blood test, weight and blood pressure) carried out locally at their GP practice or at a nearby dialysis centre and make the test results available through myhealth@QEHB before each video clinic appointment. At each appointment, patients will log in to myhealth@QEHB and speak to their consultant via an embedded video link or voice call (depending on their internet bandwidth). Video clinics will use the secure system Vidyo as the videoconferencing platform. In addition to having their follow-up appointment via myVideoClinic, the system will allow patients to submit up to three questions or topics prior to their appointment that they would like to discuss with their clinician, and patients will be able to access an audio recording of the video clinic from their patient record after each appointment.

If there are any technical issues with myVideoClinic during a video appointment, the consultant will telephone the patient to finish the appointment and schedule a face-to-face appointment if necessary. All instances where appointment rescheduling has occurred will be recorded by the clinician. If patients in the intervention group experience any technical problems with myVideoClinic during the study, they are advised to contact the myhealth@QEHB support team.

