### Outcome measures and data collection

Study outcomes and methods of data collection are summarised in Table 1.

**Table 1 Tab1:** Outcome measures, data collection instruments and format

Outcome measure	Data collection instrument	Format
Primary outcome		
(Change in) satisfaction in the VSQ-9 domains of ‘convenience of location’, ‘getting through to the office by phone’ and ‘length of time waiting’	Modified Visit-Specific Satisfaction instrument (VSQ-9) [26] within patient questionnaire	Baseline: paper At the following timepoints, after each appointment, in electronic or paper^a^ format: 3 months (if applicable) 6 months 9 months (if applicable) 12 months
Secondary outcomes		
Patient-reported health-related quality of life	EQ-5D-5 L [31] within patient questionnaire	Baseline: paper 6 months: electronic or paper 12 months: electronic or paper
Patient satisfaction scores in the other six VSQ-9 domains	VSQ-9 [26] within patient questionnaire	Baseline: paper At the following timepoints, after each appointment, in electronic or paper^a^ format: 3 months (if applicable) 6 months 9 months (if applicable) 12 months
Routinely collected clinical outcomes	Patient records	Routinely collected metrics
Number and length of clinical contacts, and instances of appointment non-attendance	Length of appointment, phone calls, myhealth@QEHB correspondence, crossover between study arms	Routinely collected metrics Clinician reporting Case report forms
Health service use	Patient questionnaire	Baseline: paper At the following timepoints, after each appointment, in electronic or paper^a^ format: 6 months 12 months
Costs (NHS perspective and societal perspective)	Patient questionnaire and routinely collected data	Baseline: paper At the following timepoints, after each appointment, in electronic or paper^a^ format: 3 months (if applicable), 6 months 9 months (if applicable) 12 months Routinely collected metrics
MyVideoClinic system performance	Failed appointments, service outages, telephone consultations	Routinely collected metrics
Clinical tests performed locally prior to video clinic appointment	Blood tests, blood pressure and weight	Case report form completed by clinician
Patient, carer and clinician experience	Semi-structured interviews	Semi-structured interviews

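### Follow-up questionnaires, including service use and costs, are sent only relative to appointments, so an unattended or late appointment yields no new measurement at 6 or 12 months

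*Protocol article*

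**What the plan says.** The trigger is in the Follow-up section: "Patients will complete patient satisfaction and summary cost questionnaires after each myVideoClinic or standard hospital appointment". Dispatch is fixed there too: "Questionnaires will be sent to patients in both study arms electronically through the myhealth@QEHB system no more than 7 days after each appointment". The same section gives nominal times, for example "For participants on a 6-monthly follow-up schedule, data will be collected at baseline and at 6 and 12 months", and says that the 6- and 12-month questionnaires carry the full set of satisfaction, cost, IT and HRQoL items for everyone.

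Table 1 merges time point and visit. Its rows for the VSQ-9, health service use and costs all read "At the following timepoints, after each appointment, in electronic or paper^a^ format". The EQ-5D-5L row lists only baseline, 6 and 12 months, with no reference to an appointment. The Table 1 footnote offers paper forms, but only to patients who have technical trouble answering electronically.

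On timing, Recruitment and consent says "Once recruited, participants will stay in the study for 12 months" and leaves appointment frequency to clinical need. The primary outcome section sets the 10-point threshold at 12 months.

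The plan expects appointments to go wrong. Table 1 counts "instances of appointment non-attendance" and failed video appointments among the outcomes. If the video link fails, "the consultant will telephone the patient to finish the appointment and schedule a face-to-face appointment if necessary".

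In Statistical analysis, a missing end-of-study VSQ-9 is replaced by the patient's most recent value.

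**The concern.** The VSQ-9 rates a visit, so tying it to appointments is natural. Service use, costs and quality of life over a period do not need a visit, yet under the stated dispatch rule a patient who misses the 6- or 12-month appointment is never asked about them. Patients who miss appointments may well differ in service use and costs from those who attend, and data that were never requested cannot be recovered in the analysis.

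For the primary outcome, the 12-month comparison depends on an appointment that the study does not schedule and that, for a 6-monthly patient, falls at the edge of the participation period. If it is missed or late, the analysis uses an older value. The plan also does not say expressly whether a video appointment finished by telephone triggers a questionnaire. That uncertainty exists in the video arm only.

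**Working it through.** **1. Does any rule produce a questionnaire without an appointment?**

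| Item | Trigger in Table 1 | Dispatch in Follow-up | Fallback shown if no appointment |
|---|---|---|---|
| VSQ-9 | time point, after the appointment | within 7 days of the appointment | last value carried forward |
| Health service use | time point, after the appointment | same | none |
| Costs, patient-reported | time point, after the appointment | same | none (routine data supply part of the costs) |
| EQ-5D-5L | 6 and 12 months only | same, as part of the 6- and 12-month questionnaires | none stated; Table 1 implies calendar dispatch |

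For the first three rows the answer is no. For the EQ-5D-5L, Table 1 and the Follow-up section do not agree.

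**2. Timing.** A 6-monthly patient has two follow-up appointments, at months 6 and 12. If each interval runs one week late (an assumption), the second falls 2 × 1 = 2 weeks after month 12. Even an on-time appointment may have its questionnaire sent up to 7 days later.

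**3. What replaces a missing 12-month VSQ-9.** On a 3-monthly schedule it is the month-9 value, if there is one. On a 6-monthly schedule it is the month-6 value. With no follow-up value it is baseline.

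**4. The plan's own numbers.** The stated size is 90 per group, from 62 per group and 30% attrition. 62 / (1 − 0.30) = 88.6, so 89, which agrees with 90 to within rounding. No SD is given. With two-sided alpha 0.05 (sidedness is assumed) and 80% power, 62 per group implies SD = 10 × √(62/2) / (1.960 + 0.842) ≈ 19.87. The 30% is applied to both arms alike. It protects numbers, not comparability.

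**5. Effect on the primary comparison.** Let f be the share of an arm whose value is carried forward, and b the mean of the carried value minus the value that would have been recorded. Then

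shift in the difference = f(video) × b(video) − f(control) × b(control).

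The documents give neither f nor b. Assume a true 10-point effect and f(control) × b(control) = 0:

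| f(video) | Baseline carried forward, b = −10 | Earlier value 20 points too high, b = +20 |
|---|---|---|
| 5% | −0.5, difference 9.5 | +1.0, difference 11.0 |
| 10% | −1.0, difference 9.0 | +2.0, difference 12.0 |
| 20% | −2.0, difference 8.0 | +4.0, difference 14.0 |

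The sign changes with b. Equal f and equal b in the two arms cancel.

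For the baseline column, with all 90 per arm analysed and SD 19.87, power = Φ(difference / (19.87 × √(2/90)) − 1.96). This gives 0.92 with nothing carried forward, then 0.89, 0.86 and 0.77 at 5%, 10% and 20%.

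**The case against.** The strongest reply is that the text covers more than it first appears to.

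- **Telephone completion.** The call is made to finish the appointment, and the service already allows a voice call. Nothing withholds the questionnaire. This stands; what remains is that the trigger is not spelled out.
- **Rebooked visits.** A reader might infer that a replacement hospital visit hides a failed video attempt. The intervention is the option of video, face-to-face attendance is not a withdrawal, and the analysis is by intention to treat. Rating the replacement visit fits that design.
- **Pro-video bias.** A reader might infer that the worst video episodes drop out and the comparison therefore favours video. The documents do not support this. Patients with a missing end-of-study VSQ-9 stay in the analysis with an earlier value, and a carried baseline would dilute a benefit. Non-attendance and slippage are not confined to one arm.
- **Hard stop at month 12.** No text discards a late questionnaire, and dispatch up to 7 days after a month-12 visit suggests some tolerance. A strict cut-off is an inference. Visit windows are also detail that an article may leave to the full protocol, and the figure of time points is not shown.
- **EQ-5D-5L.** Table 1 and the secondary outcomes section support calendar collection, so its loss with a missed appointment is not established. The conflict with the dispatch rule remains.
- **VSQ-9 after non-attendance.** A visit-specific instrument has little to rate when no visit took place. This stands, and the fix does not ask for it.

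None of this supplies a 6- or 12-month request for service use and patient-reported costs when the appointment is missed. That is a trigger the article states, not a detail it omits.

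**Conclusion.** The point holds in a limited form. The VSQ-9, health service use and cost questionnaires are dispatched only relative to appointments whose timing the study does not control, and the dispatch rule does not match the EQ-5D-5L row of Table 1. An unattended or late appointment gives no new measurement. For the primary outcome the result is an older value, possibly baseline; for patient-reported service use and costs no replacement is shown.

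The problem can arise in both arms, with only video-link failure specific to the video arm. Neither the direction nor the size of any bias can be derived from the documents. The 9-point and 12-point results at 10% are illustrations that rest on assumed shares and scores, an SD back-calculated from the sample size, and no net shift in controls. The case for acting is that the change is cheap and the missing data are avoidable, not that a bias has been shown.

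**What to change.** 1. Send the EQ-5D-5L, health service use and cost questionnaires to all participants at 6 and 12 months from randomisation, whether or not an appointment took place, and align the Follow-up section and Table 1 with this.
2. State that a video appointment finished by telephone triggers the VSQ-9.
3. State that the VSQ-9 from the end-of-study appointment is accepted even if that appointment slips past month 12.

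The cost is a change to the portal's questionnaire triggers and slightly later last data. No extra visits are needed. If the 12-month participation period is meant strictly, the third item needs a short wording change to that period.

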### Qualitative study

In accordance with Medical Research Council guidelines for evaluating complex interventions [35], an embedded qualitative study will explore patient, carer/family member and healthcare professionals’ experiences and perceptions of myVideoClinic. Semi-structured interviews will be undertaken with the following groups:Patients randomised to the standard care group (*n* = 4)Patients randomised to myVideoClinic (intervention) group (*n* = 8)Carers/family members of patients in the intervention and control groups (*n* = 6)Patients who did not wish to take part in the randomised evaluation (*n* = 4)Healthcare professionals involved in the care of the intervention patient group (*n* = 14)

#### Patients

Patients randomised to the intervention group will be stratified according to their degree of engagement with the intervention (patients completing 50% or fewer of their scheduled video clinic appointments vs. those completing more than 50%). Patients will be purposively sampled to ensure diversity on key variables such as age and sex. Selected patients will be invited to take part in a semi-structured interview to explore their opinions or experiences of using the myVideoClinic and any suggestions on how it could be improved at the end of their involvement in the study (*n* = 8). Purposively sampled patients in the control group (*n* = 4) will also be interviewed about their experiences of participating in the study.

#### Carers/family members

Carers/family members of patients being interviewed at the end of the study (*n* = 6) will be invited to take part in an interview to explore their experiences of caring for/living with a patient in the video clinic study and any impact of study participation on them.

#### Patients who do not wish to take part in the randomised evaluation

A small number of eligible patients (*n* = 4) who decline participation in the study will be interviewed to discuss their reasons for not taking part. This will provide important information that may inform the subsequent rollout of video clinics to other clinical specialties or sites if the intervention is found to be effective.

#### Health professionals

A purposive sample of 14 health professionals (clinicians who administer consultations, *n* = 8; staff who administer clinical tests at the hospital, *n* = 2; primary care staff administering clinical tests locally, *n* = 4) will be interviewed at the end of the study. Interviews will explore staff experiences of the myVideoClinic system, including any perceived advantages (e.g. cost, time and quality of care) and disadvantages (e.g. lack of physical examination). Interviews will provide information on how best to engage and support health professionals in adopting video clinics within routine care if the intervention is considered effective.

### Sample size and study power

The sample size for the study has been determined by the effect size needed to detect a clinically significant (10 point) difference between intervention and control groups in the primary outcome measure (patient satisfaction as measured on three domains of the VSQ-9). Assuming a normal distribution of satisfaction scores, a sample size of 62 patients per group would be sufficient to detect a 10-point difference in VSQ-9 scores between groups at 80% power and an alpha of 0.05. Over a 12 month period, an estimated 267 eligible patients will be available for recruitment to the study from the four liver clinics of interest. Annually, approximately 1% of liver transplant patients at UHB undergo a re-transplant and 2% die. Thus, around 21 patients per month will be eligible for recruitment. Audit data collected from one liver clinic in early 2017 suggest that approximately 60% of eligible patients will be willing to participate in the study (13 per month). A previous randomised controlled study of video clinics in diabetes care reported an attrition rate of 30% [12]. Applying this attrition rate to our patient sample, and allowing for participant withdrawals, missing data and losses to follow-up, the required sample size for the study is 90 per group (*n* = 180 total). Recruiting at a rate of 13 patients per month, we anticipate recruitment to take approximately 14 months in total (Fig. 3).

**Fig. 3 Fig3:**
[figure not shown]
Recruitment rate

### Statistical analysis

An interim analysis will be undertaken once 25% of the target recruitment sample have completed two appointments. This interim analysis will focus on crossover from the intervention to control groups due to patients being unable to complete their clinical testing locally. The findings from this interim analysis will be discussed with the study’s independent monitoring group as high rates of crossover have implications for the feasibility of the intervention and will reduce study power to detect significant differences between intervention and control arms in the outcomes of interest. The main data analysis will be undertaken on an intention-to-treat basis, although an unblinded per protocol analysis will also be performed for the primary outcome measure to assess whether similar results are obtained with regard to any statistically significant findings. It is acknowledged that younger patients may potentially find the intervention more beneficial due to greater familiarity with technology, so age will be controlled for and a sensitivity analysis will assess whether age has an independent effect on outcomes.

The characteristics of study participants at baseline will be summarised descriptively, with comparison of proportions tests used to assess any differences between intervention and control groups on the basis of sociodemographic and clinical characteristics. Analysis of the primary outcome measure (difference between groups in scores in three domains of the VSQ-9) will use independent *t* tests if data are normally distributed. If data are not normally distributed, the Mann–Whitney U test will be used. For patients with missing end-of-study VSQ-9 data, their most recently collected data will be used in the analysis. If participant numbers allow, subgroup analysis will assess patient satisfaction scores adjusting for the level of engagement that intervention patients had with myVideoClinic (i.e. those with 6 months or less of video clinic appointments vs. those with more than 6 months of video clinic appointments).

Secondary outcome measures will be analysed descriptively where the same data have been collected from patients in both study arms (e.g. health service use). Where secondary outcome data are relevant to the intervention group only (e.g. the incidence of technical issues during myVideoClinic appointments), these will be tabulated and basic statistical analyses performed (numbers, percentages, means/medians etc.). Attrition/withdrawal rates and rates of questionnaire completion will be analysed for both study arms and overall. Analysis of HRQoL data will follow the recommendations in the EQ-5D-5 L User Guide [34]. Health state valuations will be calculated for each profile based on pre-calculated scoring coefficients. Changes in HRQoL between baseline and study end will be assessed for each patient and both descriptive and comparative analyses will be performed to compare HRQoL between participants in the intervention and control groups.

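### The age analysis is motivated by a benefit that may vary with age, but the planned check addresses age's own association with satisfaction and cannot separate the two

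*Protocol article*

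**What the plan says.** The protocol article, Statistical analysis, gives its reason for looking at age: "younger patients may potentially find the intervention more beneficial due to greater familiarity with technology". The same sentence continues with the response: age is to be adjusted for, and "a sensitivity analysis will assess whether age has an independent effect on outcomes".

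The rest of the section bears on age as follows:

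- The primary comparison "will use independent *t* tests if data are normally distributed", with the Mann–Whitney U test otherwise. Neither has a covariate.
- The one subgroup analysis named is by use of the intervention, not by age: "subgroup analysis will assess patient satisfaction scores adjusting for the level of engagement that intervention patients had with myVideoClinic".
- No arm-by-age comparison is described in this section or elsewhere in the article.

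Age is recorded for every participant at baseline (Data collection time points, Baseline).

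**The concern.** The reason given is effect modification: the gain from video over face-to-face care may be larger at younger ages. The analyses given in response are adjustment and a test of age's own effect. Adjustment yields a single arm difference averaged over age. Randomisation already balances age in expectation, so adjustment mainly adds precision. A test of age's own effect asks whether satisfaction differs between younger and older patients, whichever arm they are in.

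At stake is a misreading. A significant age effect could be reported as showing that younger patients benefit more, when older patients are simply less (or more) satisfied in both arms. A null age effect could be reported as showing that benefit does not depend on age, when it does.

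**Working it through.** **Inputs from the protocol (Sample size and study power).** The target difference is 10 points, "at 80% power and an alpha of 0.05", with 62 per group before attrition, 30% attrition and 90 per group recruited. No SD is given and sidedness is not stated. Two-sided testing is assumed.

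**Reproducing the plan's figure.** The formula is n per group = 2 × (1.960 + 0.842)² × SD² / 10².

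- At SD 20 this is 2 × 7.85 × 4 = 62.8, so 63. Solving back from 62 gives SD 19.9 (22.4 if one-sided).
- 62 / 0.70 = 88.6, so 89, against 90 stated. 90 × 0.70 = 63 evaluable per arm.

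The stated figures are consistent with an SD near 20. I use SD 20 with a range of 15 to 25.

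**What each test estimates.** Let the age slope (points per SD of age) be b0 in control and b1 in video. With equal arms, the age effect in a model without an interaction is about (b0 + b1)/2. The change in video benefit with age is b1 − b0. These are different quantities.

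**Simulation.** Settings: 62 per arm, SD 20, standardised age, 3,000 runs per case, 5% two-sided tests. The slopes are assumptions chosen to illustrate.

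| Case | b0, b1 | Average slope | Difference in slopes | Age main effect significant | Interaction significant |
|---|---|---|---|---|---|
| No age effect | 0, 0 | 0 | 0 | 5.1% | 4.9% |
| Same age effect in both arms | −6, −6 | −6 | 0 | 90% | 5.6% |
| Offsetting slopes | +5, −5 | 0 | −10 | 5.0% | 78% |
| Age matters only in the video arm | 0, −10 | −5 | −10 | 75% | 78% |

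Rows two and four both usually give a significant age effect, yet only row four has differential benefit. Row three has the same differential benefit as row four, and the age main effect does not see it. A difference of 10 points per SD of age is large: about 16 points between the younger and older halves (10 × 1.6, see below).

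**Precision of the interaction, age continuous.** SE per SD of age = SD × √(2/63):

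- SD 15: 2.7, 95% CI about ±5.2
- SD 20: 3.6, 95% CI about ±7.0
- SD 25: 4.5, 95% CI about ±8.7

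**Precision with a median split of age.** The SE of the difference in arm effects between halves is SD × √(4/31.5), which is 7.13 at SD 20. This is on another scale. If age is roughly normal, the means of the two halves lie 2 × √(2/π) = 1.6 SD apart, so the SE per SD of age is 7.13 / 1.6 = 4.5. Against 3.56 that is about 25% larger.

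**Power, two equal age halves, 63 per arm.** For a 10-point difference in arm effect between halves, power is about 29% at SD 20 (46% at SD 15, 20% at SD 25). The difference detectable with 80% power is about 20 points (15 to 25).

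**The case against.** The best defence is that the sentence is loosely worded in a condensed article. It names no regression model for age, and since it opens with differential benefit, the check may be meant to include it. The exact model terms can be left to an analysis plan that is not shown. That stands as far as detail goes. It does not remove the point: the article states both the question and the check, and the ordinary meaning of an independent effect of age is a main effect adjusted for other terms. If an interaction was meant, the wording needs correcting.

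A second defence is that if familiarity with technology matters only for video users, the main-effect test will often be significant. This also stands. A reader might infer that the planned check carries no information about differential benefit, and that is too strong: in the video-arm-only case it is significant in 75% of runs, close to the 78% for the interaction. A main effect can arise from an interaction but cannot identify one. The offsetting case needs opposite slopes in the two arms, and nothing in the protocol suggests these are likely.

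Third, the interaction would have little power. That is true, and it argues for reporting an estimate with its interval. It does not argue for testing a different quantity.

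Fourth, age is not among the stated aims, and the protocol does not link age to who would be offered video clinics later. This limits the consequence.

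**Conclusion.** The concern holds in a limited form. The stated age check does not answer the question given as its reason, because it cannot tell a general age effect from a video benefit that varies with age. That conclusion follows from what the tests estimate and does not depend on the SD. The precision and power figures do depend on assumptions: SD 15 to 25, about 63 evaluable per arm, two-sided tests and, for the median split, roughly normal age.

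Two stronger readings are not supported. A reader might infer that the trial's main result is compromised. It is not, because the primary randomised comparison does not use the age check. A reader might also infer, from standard errors of 3.6 and 7.1 at SD 20, that a median split doubles the uncertainty. Those figures are on different scales, and the like-for-like loss is about 25%.

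**What to change.** Replace the check on an independent effect of age with a pre-specified exploratory linear regression of the primary VSQ-9 score on arm, age (continuous) and arm-by-age. Report the interaction with its 95% CI and the estimated arm difference at, for example, the 25th and 75th percentiles of age. State that the result is an estimate and not a definitive test.

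Because the stated primary test has no covariate, the plan must also say which model gives the age-adjusted comparison. If age is to be controlled for, use the same linear model without the interaction for that purpose.

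The cost is one small regression model and a few sentences. No new data are needed, since age is already collected at baseline, and the sample size does not change.
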